### B 4.3 Bruising

Only Study COV005 collected bruising as a solicited AE. Severity grading within the diary consisted of Grades 1 (< 10 mm), 2 (10-25 mm), and 3 (> 25 mm). For the sake of completeness, these results will be presented within the pooled data output.

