### 10.1.3 Solicited AEs

Diary cards will collect the timing and severity of predefined Solicited AEs listed in [Appendix B](#). Solicited local AEs and solicited systemic AEs collected for 7 days (Day 0 to Day 6 for COV005 while Day 0 to Day 7 for rest of studies) after vaccination for each dose will be summarized respectively. The strategy for pooling the data across different studies is provided in [Appendix B](#).

Each solicited AE will be summarized by treatment group at the following time intervals: Days 0-7, and Days 0 to day 7 individually (for PA only). Each time interval will be repeated for after dose 1, after dose 2 and after any dose. For each time interval, the count and percentage of participants will be determined for each of the following categories: participants evaluated, participants with any event, mild events, moderate events, severe events, and potentially life-threatening events. Participants should not be double counted; therefore, the event of greatest severity will be used for participants with more than one episode of the same event. Similar counts and percentages will be presented for solicited local AEs “Overall” and solicited systemic AEs “Overall”. For participants evaluated for diary cards, missing values will be treated as missing in the calculation.

A listing of all solicited AEs will be provided at the time of the primary analysis.

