### B 4.2 Redness, Swelling, and Induration

Redness and swelling will be reported in millimeters in all 4 studies, and all 4 CSPs contain the same severity grading ([Table B4](#)). (Note: the source data are recorded in millimeters but the grading criteria use centimeter; unit conversion will be required).

Induration will also be reported in millimeters in Studies COV001, COV002, and COV003 with the same protocol-defined severity grades, in centimeters. However, in Study COV005, induration is reported in the patient diary at 3 severity grade levels (mild, moderate, severe) that are not compatible with the millimeter measurements used in the other 3 studies.

Based upon the above, redness and swelling can be pooled across all 4 studies, and induration can be pooled across Studies COV001, COV002, and COV003.

| Table B4 CSP-specified Severity Grading and Patient Diary Measurements for Redness, Swelling, and Induration |                                                        |                                  |                                                                  |
|---------------------------------------------------------------------------------------------------------------------|--------------------------------------------------------|----------------------------------|------------------------------------------------------------------|
| Event                                                                                                        | CSP-specified grading severity                  | Patient diary measurement |                                                                  |
| Study                                                                                                        | COV001, COV002, COV003, COV005                  | COV001, COV002, COV003    | COV005                                                    |
| Redness                                                                                                             | Grade 1: 2.5-5 cm                                      | Millimeter                       | Millimeter                                                       |
|                                                                                                                     | Grade 2: 5.1-10 cm                                     |                                  |                                                                  |

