|                                                                                                                     | Grade 3: > 10 cm                                       |                                  |                                                                  |
|                                                                                                                     | Grade 4: Necrosis or exfoliative dermatitis            |                                  |                                                                  |
| Swelling                                                                                                            | Grade 1: 2.5-5 cm and does not interfere with activity | Millimeter                       | Millimeter                                                       |
|                                                                                                                     | Grade 2: 5.1 - 10 cm or interferes with activity       |                                  |                                                                  |
|                                                                                                                     | Grade 3: > 10 cm or prevents daily activity            |                                  |                                                                  |
|                                                                                                                     | Grade 4: Necrosis                                      |                                  |                                                                  |
| Induration                                                                                                          | Grade 1: 2.5-5 cm and does not interfere with activity | Millimeter                       | Grade 1: small hard lumps/swelling felt, smaller than 25 mm      |
|                                                                                                                     | Grade 2: 5.1 - 10 cm or interferes with activity       |                                  | Grade 2: hard lump/swelling felt, larger than 25 mm              |

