| Itch                                                                                         | X                                           | X      | X      | X      | Grade based upon Studies COV001/COV002 grading criteria. Study COV005 scale lacks grade 4          |
| Swelling                                                                                     | X                                           | X      | X      | X      | Grade based upon common objective grading criteria (diameter)                                      |
| Induration                                                                                   | X                                           | X      | X      | -      | Grade based upon the common objective grading criteria. Study COV005 grading scale not compatible. |
| Bruising                                                                                     | NA                                          | NA     | NA     | X      | Included despite recorded in only one study so that all available data are included.               |
| Solicited systemic adverse events                                                            |                                             |        |        |        |                                                                                                    |
| Fever                                                                                        | X                                           | X      | X      | X      | Grade based upon Studies COV001/COV002/COV003 grading criteria.                                    |
| Feverishness                                                                                 | X                                           | X      | X      | -      | Grade based upon Studies COV001/COV002 grading criteria. Study COV005 has no severity grading      |
| Chills                                                                                       | X                                           | X      | X      | -      | Grade based upon Studies COV001/COV002 grading criteria. Study COV005 has no severity grading.     |
| Joint pain                                                                                   | X                                           | X      | X      | X      | Grade based upon Studies COV001/COV002 grading criteria. Study COV005 scale lacks Grade 4          |

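### Bruising, recorded only in COV005 and Grade 3 from just over 25 mm, is not kept out of the pooled solicited local Overall severity rows, where redness of the same size is mild

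*SAP*

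**What the plan says.** Appendix B 4.3 states: "Only Study COV005 collected bruising as a solicited AE". It gives the diary scale as "Severity grading within the diary consisted of Grades 1 (< 10 mm), 2 (10-25 mm), and 3 (> 25 mm" and adds: "For the sake of completeness, these results will be presented within the pooled data output".

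Table B8 (Appendix B 6), which sets out what each study contributes to the overall pool, lists bruising under solicited local adverse events. COV005 is marked as contributing and the other three studies as not available. The comment reads: "Included despite recorded in only one study so that all available data are included".

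Table B4 (Appendix B 4.2) grades the other size-based local events. For redness the first step is "Grade 1: 2.5-5 cm", and Grade 3 lies above 10 cm. For swelling and induration it is "Grade 1: 2.5-5 cm and does not interfere with activity", with Grade 3 above 10 cm or when daily activity is prevented.

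Section 10.1.3 refers to Appendix B for the list of solicited events and the pooling strategy. It counts participants by mild, moderate, severe and potentially life-threatening events, then says: "Similar counts and percentages will be presented for solicited local AEs" taken Overall. No sentence removes bruising from that Overall summary or regrades it.

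**The concern.** The Overall local table puts each participant in a severity category according to the worst local reaction. That is readable only if a given grade means roughly the same thing across the components. Bruising is measured in millimetres, like redness and swelling, but on a scale whose top grade begins where theirs only starts. It is also available from one study only.

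The SAP recognises this kind of problem elsewhere. COV005 fever is regraded to the scale of the other three studies (B 4.1). COV005 induration is left out because its diary scale does not match the millimetre measurements (B 4.2, Table B8). COV005 feverishness and chills are left out because they carry no grades (B 5.2). Bruising is kept in for completeness, with no statement that its scale is comparable. What is at stake is the meaning of the pooled severe-local percentage in each arm, a prominent line in a reactogenicity summary.

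**Working it through.** The SAP states no figure to reproduce here. The check applies the two scales to the same diameters and then follows the tabulation rule.

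**Inputs.** Bruising (B 4.3): Grade 1 below 10 mm, Grade 2 at 10-25 mm, Grade 3 above 25 mm. Redness (Table B4, cm × 10): Grade 1 at 25-50 mm, Grade 2 at 51-100 mm, Grade 3 above 100 mm. Swelling and pooled induration have the same size cut-offs, and interference with activity can raise their grade.

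| Diameter | Bruise | Redness |
|---|---|---|
| 5 mm | 1 | none |
| 20 mm | 2 | none |
| 25 mm | 2 | 1 |
| 26-50 mm | 3 | 1 |
| 51-100 mm | 3 | 2 |
| above 100 mm | 3 | 3 |

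The gap is two grades from 26 to 50 mm and one grade from 51 to 100 mm. The Grade 3 cut-off for bruising is 25/100, one quarter of that for redness.

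**Following the rule.** Bruising is in the Table B8 pool of local events, and Section 10.1.3 builds the Overall local table from that pool with no exclusion. Two links are inferred:
- Grade 3 is taken to mean severe. Table 8, the COV005 grading table, heads Grade 3 that way, and B 4.2 describes the three COV005 induration levels as mild, moderate and severe.
- The greatest-severity rule is worded for repeated episodes of the same event. It reaches the Overall row through the word similar in "Similar counts and percentages will be presented for solicited local AEs".

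**Illustrative size.** The SAP gives neither bruising rates nor final diary numbers. Planned enrolment (Table 1) and the diary subsets in Section 10.1.1 give a range, with COV001 at 1122, COV003 at 200 and COV005 at 2070:
- COV002 at 3000, the stated maximum subset of its efficacy groups: 2070 / (1122 + 3000 + 200 + 2070) = 2070 / 6392 = 32%.
- COV002 at its full planned 12390: 2070 / (1122 + 12390 + 200 + 2070) = 2070 / 15782 = 13%.

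Added pooled severe-local rate = COV005 share × proportion of COV005 participants with a bruise above 25 mm and no other severe local event. For each 1%, this is 0.13 × 1% = 0.13 to 0.32 × 1% = 0.32 percentage points.

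**The case against.** The strongest reply is that B 4.3 promises only that "these results will be presented within the pooled data output", which also fits a stand-alone row. No sentence says that bruising feeds the Overall severity rows. That is fair, so the point rests on a literal reading rather than a stated rule. But Table B8 lists bruising in the pool without qualification, and a programmer following Section 10.1.3 would include it. If that is not intended, the SAP needs to say so.

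A second reply is that the composite already mixes scales. COV005 itching is severe when it needs a soothing cream, and it is pooled. There, however, B 5.3 explicitly judges the scales similar enough. No such judgement is made for bruising, which would be hard to defend against Table B4.

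A third reply is that bruising is a genuine solicited event in COV005, so removing it from the any-event count would drop real data. This stands, and the fix respects it.

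A reader might also infer more than the SAP supports:
- That the AZD1222-versus-control contrast shrinks. Nothing in the SAP shows that bruises occur equally in both arms. If they did, adding d to both rates leaves the difference unchanged: (a + d) − (b + d) = a − b. A ratio would move, but Section 10.1.3 plans only counts and percentages.
- That COV005, and so South Africa, would look more locally reactogenic. COV005 contributes no pain, warmth or pooled induration, so it has five local components (tenderness, redness, itch, swelling, bruising) against seven elsewhere. Its net position is unknown.

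**Conclusion.** The point holds for the severity rows of the pooled solicited local Overall summary. As written, a 26-50 mm bruise counts as severe beside redness of equal size counted as mild, contrary to how the SAP treats COV005 fever and induration. The consequence is a pooled severe-local percentage in each arm that partly reflects bruises from one saline-controlled study.

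The size cannot be computed from the SAP. The figure of 0.13-0.32 percentage points per 1% of COV005 participants affected assumes a COV005 share of 13-32% of diary participants, equal in both arms. That share is rough: the 2070 includes the HIV group that Section 5 excludes, and the 12390 includes groups excluded from the pool.

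The separate bruising row is transparent and is not at fault. The issue is descriptive and confined to safety reporting; no efficacy result or planned test is affected. It should be corrected before the tables are programmed.

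**What to change.** State in B 4.3, Table B8 and Section 10.1.3 that bruising is shown as its own COV005-only row, with COV005 diary participants as the denominator, and does not contribute to the mild, moderate or severe rows of solicited local AEs Overall. It may remain in the Overall any-event row, with a footnote saying that only COV005 collected it. Regrading to Table B4 is not an option on what the SAP describes, because the top bruising category is open above 25 mm.

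The cost is one sentence in each place and one programming exclusion. The downside is that one solicited event is missing from the composite severity rows, though it is still reported in full, with its grades, in its own row.

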### B 5 Pooling of Solicited Adverse Events with Subjective Measurements

This section presents events that will be reported by participants using subjective severity grades.

### B 5.1 Pain and Warmth at the Injection Site, Malaise, Nausea, and Vomiting

Pain and warmth at the injection site and malaise, nausea, and vomiting will be reported in Studies COV001, COV002, and COV003. (Study COV005 did not include vomiting in the protocol and did not collect pain and warmth at the injection site and malaise and nausea despite being specified in the protocol.) Common severity grades are used in Studies COV001 and COV002 ([Table B5](#)). The severity grades in Study COV003 are somewhat different but similar enough to justify pooling of these 4 solicited AE across all 3 studies.

| Table B5 Patient Diary Severity Grades for Pain and Warmth at Injection Site, Malaise, Nausea, and Vomiting Events in Studies COV001, COV002, and COV003 |                                                              |                                                                                                                                                  |
|-----------------------------------------------------------------------------------------------------------------------------------------------------------------|--------------------------------------------------------------|--------------------------------------------------------------------------------------------------------------------------------------------------|
| Severity                                                                                                                                                 | COV001, COV002                                        | COV003                                                                                                                                    |
| Grade 1                                                                                                                                                         | Mild: easily tolerated with no limitation on normal activity | Mild: transient or mild discomfort (< 48 hours); no interference with routine activities; no medical intervention/therapy required               |
| Grade 2                                                                                                                                                         | Moderate: some limitation of daily activity                  | Moderate: mild to moderate limitation in routine activities – some assistance may be needed; no or minimal medical intervention/therapy required |
| Grade 3                                                                                                                                                         | Severe: unable to perform normal daily activity              | Severe: marked limitation in routine activities, some assistance usually required; medical intervention/therapy required                         |
| Grade 4                                                                                                                                                         | Emergency department or hospital admission required          | Potentially life-threatening: requires assessment in accident & emergency department or hospitalization                                          |

### B 5.2 Feverishness and Chills

Feverishness and chills will be reported with common severity grades in Studies COV001 and COV002, slightly different severity grades in Study COV003, and a binary “yes” or “no” without severity grading in Study COV005 ([Table B6](#)). The severity grades used in Studies COV001, COV002, and COV003 are similar enough to justify pooling of these 2 solicited AEs across the 3 studies. The lack of severity grading of these events in Study COV005 precludes them being pooled with the other studies.

| Table B6 Patient Diary Severity Grades for Feverishness and Chills in Studies COV001, COV002, and COV003 |                                                              |                                                                                                                                                  |                             |
|-----------------------------------------------------------------------------------------------------------------|--------------------------------------------------------------|--------------------------------------------------------------------------------------------------------------------------------------------------|-----------------------------|
| Severity                                                                                                 | COV001, COV002                                        | COV003                                                                                                                                    | COV005               |
| Grade 1                                                                                                         | Mild: easily tolerated with no limitation on normal activity | Mild: transient or mild discomfort (< 48 hours); no interference with routine activities; no medical intervention/therapy required               | Yes/No
(without grading) |
| Grade 2                                                                                                         | Moderate: some limitation of daily activity                  | Moderate: mild to moderate limitation in routine activities – some assistance may be needed; no or minimal medical intervention/therapy required |                             |
| Grade 3                                                                                                         | Severe: unable to perform normal daily activity              | Severe: marked limitation in routine activities, some assistance usually required; medical intervention/therapy required                         |                             |
| Grade 4                                                                                                         | Emergency department or hospital admission required          | Potentially life-threatening: requires assessment in accident & emergency department or hospitalization                                          |                             |

### **B 5.3 Tenderness, Itching, Joint pain, Muscle pain, Fatigue, and Headache**

These solicited AEs have identical 4-level severity grading scales in Studies COV001 and COV002 and a slightly different 4-level grading scale in Study COV003 ([Table B7](#)). Study COV005 has event-specific criteria and differs further from the other studies in that a 3-point mild, moderate, and severe scale will be used for these events. The severity grades used in Studies COV001, COV002, and COV003, as discussed above, are similar enough to justify pooling of these 6 solicited AEs across all 3 studies. In addition, the 3-level event-specific severity grades used in Study COV005 do define mild, moderate, and severe events and are also judged to be similar enough to justify pooling across studies.

| Table B7 Patient Diary Severity Grading for Tenderness, Itching, Joint Pain, Muscle Pain, Fatigue, and Headache by Study |                                                                                                                                                  |                                                                                                         |                                                   |                                                                       |                                                               |                                               |                                                                                         |
|---------------------------------------------------------------------------------------------------------------------------------|--------------------------------------------------------------------------------------------------------------------------------------------------|---------------------------------------------------------------------------------------------------------|---------------------------------------------------|-----------------------------------------------------------------------|---------------------------------------------------------------|-----------------------------------------------|-----------------------------------------------------------------------------------------|
| COV001, COV002                                                                                                           | COV003                                                                                                                                    | COV005                                                                                           |                                                   |                                                                       |                                                               |                                               |                                                                                         |
| All events                                                                                                               | All events                                                                                                                                | Tenderness                                                                                       | Itching                                    | Joint pain                                                     | Muscle pain                                            | Fatigue                                | Headache                                                                         |
| Mild: easily tolerated with no limitation on normal activity                                                                    | Mild: transient or mild discomfort (< 48 hours); no interference with routine activities; no medical intervention/therapy required               | Mild: minor tenderness when injection site is touched                                                   | Mild: minor itching                               | Mild: mild aching                                                     | Mild aching                                                   | Minor weakness/tiredness                      | Minor headache not requiring medication                                                 |
| Moderate: some limitation of daily activity                                                                                     | Moderate: mild to moderate limitation in routine activities – some assistance may be needed; no or minimal medical intervention/therapy required | Moderate: very tender when injection site is touched                                                    | Moderate: marked itching (like new mosquito bite) | Moderate: severe aching, but able to do most activities               | Severe aching, but able to do most activities                 | Very weak/tired                               | Bad headache, but able to do most activities (with medication)                          |
| Severe: unable to perform normal daily activity                                                                                 | Severe: marked limitation in routine activities, some assistance usually required; medical intervention/therapy required                         | Severe: severe pain in the injected limb, increased when it is moved or movement of the limb is reduced | Severe: severe itching requiring soothing cream   | Severe: very severe aching, requiring medication, limiting activities | Very severe aching, requiring medication, limiting activities | Unable to do normal activities during the day | Severe headache, requiring medication and unable to do normal activities during the day |
| Emergency department or hospital admission required                                                                             | Potentially Life-threatening: requires assessment in accident & emergency department or hospitalization                                          | -                                                                                                       | -                                                 | -                                                                     | -                                                             | -                                             | -                                                                                       |

